### 11.3 Data protection

Patient data will be pseudonymised before statistically evaluation.

## **12. Therapeutical intervention and staff qualification**

### 12.1 General comments concerning intervention and treatment time:

General management on the stroke unit of all included patients follows the standards of treatment defined in the contemporary European  (European Stroke Initiative [EUSI] and European Stroke Organization [ESO]) and national guidelines.

Patients will be either randomised to Vojta therapy or conventional physiotherapy within 72 hours after stroke onset. For ethical reasons, all patients received standard physiotherapy until randomisation in case randomisation is delayed e.g. by diagnostic procedures within and up to 72 hours. Eligible patients are preferred to get their MRI or CT scan as soon as possible in order to confirm their stroke (see „Imaging“).

Treatment sessions consist of 40 minutes once daily for 7 days for all patients, including treatment, mobilization and testing on weekend if necessary. Before testing on day 9 (+/-1 day) therefore all patients will have 7 treatment sessions. Assessments will be performed by two physiotherapist (one from the Vojta- one from the control group) following the four-eyes principle. In case of disagreement in scoring, a third physiotherapist should conduct an additional assessment.

### 12.2 Therapy for control group: Conventional physiotherapy

After randomisation the control group receives conventional physiotherapy. The physiotherapy programme for the control group includes repetitive sensomotoric exercises of existing functions in the sense of a task-oriented training and movement facilitation of the restricted functions on the hemiparetic side. In addition, a balance training and gait training will be performed.

### 12.3 Therapy for interventional group: Vojta therapy

The interventional group will have Vojta therapy as physical therapy. Vojta therapy will be administered with stimulation of the breast zone, which is located between the 7th and 8th ribs, addition of other zones in order to support the activation was allowed. The starting position should be supine or lateral position with the head turned 30° in the direction of the stimulation, with the extremities lying naturally on the bed. No Vojta-therapist will treat patients allocated to the control group.

### 12.4 Qualification of physiotherapists and investigators

All physiotherapists involved in the trial must be licensed physiotherapists with a graduation (in Germany vocational education for 3 years). Physiotherapy students are not allowed to treat patients within this trial. All physiotherapists must have clinical experience for more than 2 years and have experience in treatment of stroke patients. Existence of an additional qualification as i.e. as Bobath therapist is allowed for both groups. Therapists are requested not to treat following approaches of the Bobath concept.

All physiotherapists treating the interventional group must have a certification (at least level A) of the international Vojta society as qualification (see <http://www.vojta.com>).

To minimise differences all staffs at the site were trained for both the intervention and assessments by the main investigator and the principal physical therapist. Investigators assessing the NIHSS and mRS should have a certification. For the other assessment tools no certification is required.

## **13. Imaging**

Generally, imaging is performed only within the clinical indication as used in patients with ICH or AIS. Imaging usually includes a diagnostic CT-scan on admission and a follow-up imaging, generally a MRI and if not possible a CT-scan in order to confirm stroke, to determine extent of the infarction or in case of a ICH to review ICH volume and possible complications due to space occupying effects or determine ICH etiology. Patients are eligible only after a MRI or CT proven stroke. Therefore potential eligible patients are preferred to get their MRI or CT scan as soon as possible in order to confirm their stroke. No specific additional imaging is planned within the present trial.

## **14. General Definitions:**

### Baseline characteristics:

- Atrial fibrillation: no matter since when known
- Smokers: We defined a smoker as a current smoker or a participant, who had quit smoking in the last past 2 years.
- Handeness: as reported by patient (not assessed)
- Orthopaedic disease: as reported by patient or relatives, including prior surgery on spinal column or joints, prior traumas with disturbance of mobility, chronic lumbar pain syndrome and more.
- Dysphagia will be tested by the speech therapist (yes or no).

### Acute stroke therapy:

- Treatment with recombinant tissue plasminogen activator and thrombectomy before randomisation are allowed.
- Surgical procedures (i.e. external ventricle drainage) before randomisation are allowed. Subjects must be able to sign the informed consent and to understand physiotherapeutic challenges.
- In case of deterioration with transfer to the intermediate care unit treatment will be continued there. If treatment or testing is not feasible (i.e. due to ventilation), testing should be performed one day later, if still within timeframe, otherwise testing should be cancelled. The final testing (visit 3) should then be performed as soon as the patient is testable again (if timeframe >day 10), even if he did not receive 7 treatment sessions in total.

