## **8. Predefined Outcome Measures**

### **8.1. Primary Outcome Measure:**

Improvement of postural control measured with the trunc control test (TCT) on day 9 after admission to the hospital compared to baseline (Difference in scores on TCT scale between baseline and day 9)

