### **8.2. Secondary Outcome Measures:**

(i) Improvement of neglect measured with the Catherine Bergego Scale (CBS) part 5 and 6 on day 9 after admission to the hospital compared to baseline (Difference in scores on CBS scale between baseline before treatment and day 9 after treatment)

(ii) Improvement of arm motor function measured with the motor evaluation scale for upper extremity in stroke patients (MESUPES, part 1 to 4) on day 9 after admission to the hospital compared to baseline (Difference in scores on MESUPES between before treatment and day 9 after treatment).

(iii) Improvement of stroke severity measured with the National Institute of Health Stroke Scale (NIHSS) on day 9 after admission to the hospital compared to baseline (Difference in scores on NIHSS between baseline before treatment and day 9 after treatment).

(iv) Improvement of the Barthel Index (BI) on day 9 after admission to the hospital compared to baseline (Difference in scores on BI between baseline before treatment and day 9 after treatment)

(v) Improvement of the modified Rankin Scale (mRS) on day 90 after stroke compared to baseline (Difference in scores on mRS between baseline before treatment and day 90). The 90 day mRS is assessed via telephone interview by a blinded assessor.

(vi) Improvement of the Barthel Index (BI) on day 90 after stroke compared to baseline (Difference in scores on BI between baseline before treatment and day 90). The 90 day BI is assessed via telephone interview by a blinded assessor.

(vii) Improvement of the neglect (measured with the Catherine Bergego Scale) before and after every single intervention on day 2, day 5 and day 9.

(viii) Improvement of arm motor function (measured with the MESUPES) before and after every single intervention on day 2, day 5 and day 9.

The timing for the primary endpoint was chosen at day nine, because this is the mean residence time of stroke patients in the acute clinic before discharge to a rehabilitation center.

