## 9. Timeframes for Visits Outcome Measures

- Randomisation: Maximum 72h after stroke onset
  - Test 1: on day 2 after admission to hospital (+/- 1 day)
  - Test 2: on day 5 after admission to hospital (+/- 1 day)
  - Test 3: on day 9 after admission to hospital (+/- 1 day)
  - Test 4: on day 90 after stroke onset (+/- 5 days)
- The trunc control test (TCT) will be assessed at day 2 after admission to hospital before the first treatment (baseline), at day 5 and day 9 after treatment.
  - The National Institutes of Health Stroke Scale (NIHSS) will be assessed at day 2 after admission to hospital before the first treatment (baseline) and at day 9 after treatment.
  - The Catherine Bergego Scale (CBS) and the Motor Evaluation Scale for Upper Extremity in Stroke Patients (MESUPES) will be assessed at day 2, day 5 and day 9 after admission before and after treatment.
  - The modified Rankin Scale (mRS) and the Barthel Index (BI) will be assessed at day 2 after admission to hospital before the first treatment (baseline), at day 9 after treatment and at day 90 after stroke onset via a phone interview.
  - Investigators will record the occurrence of any serious adverse event and other safety outcomes that occur during hospital admission up to day 90.

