## 10. Outcome Assessments

### 10.1 Detailed description of assessment tools

#### *(i) Trunc Control Test (TCT)* 

The TCT examines 4 items of axial movements:

- 1) rolling from a supine position to the weak side;
- 2) rolling from a supine position to the strong side;
- 3) sitting up from a lying-down position; and
- 4) sitting in a balanced position on the edge of the bed with feet off the ground for 30 seconds.

For each item can be scored 0, 12 or 25 points:

- 0= unable to perform movement without assistance;
- 12= able to perform movement, but in an abnormal style (Examples: pulls on bed clothes or monkey pole, or uses arms to steady self when sitting);
- 25= able to complete movement normally.

For the sitting balance item, a patient scores 12 if he needs to touch anything with his hands to stay upright, and 0 if he is unable to stay up (by any means) for 30 seconds. The TCT score is the sum of the scores obtained on the four tests and ranges from 0 (minimum) to 100 (maximum and indicating better performance). The examiner's score must relate solely to the performance during the test.

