### 11.2 Statistical analysis plan

We plan an intention to treat analysis. For the primary endpoint (difference of scores in trunc control test between day 9 and baseline) an increase of 12 points (=12%) on the scale of the TCT was predefined as a meaningful difference pragmatically, due to lack of data in the literature, because an improvement of 12 points in the TCT indicates a clinical relevant improvement of self-dependence (i.e. no more need of an auxiliary person, no more need for an adjuvant as edge of bed for moving). Normal distribution of the variables will be tested by the Shapiro-Wilk-test. For the primary endpoint we assume non-Gaussian distribution and we plan an analysis of variance with the non-parametric Mann–Whitney-U-test. The primary endpoint (difference of scores in trunc control test between day 9 and baseline) will be tested concerning the influencing factors a priori known to potentially affect outcome (age, sex, NIHSS > or <10 at baseline; stroke site, thrombolysis and thrombectomy) to test whether they affected the treatment. Complications occurring between baseline and day 9 will be analyzed with the exact Fisher Test. An interim analysis is not planned. We have not defined any discontinuation criteria. Statistical analysis will be made by the principal investigator with support of a statistical institute.

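### The deterioration rule lets the primary TCT be taken at any time after day 10, against the day 9 (±1) definition, so deterioration in one arm can be masked by later recovery

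*Protocol*

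**What the plan says.** Section 8.1 defines the primary outcome as "Difference in scores on TCT scale between baseline and day 9". Section 9 gives the window: "Test 3: on day 9 after admission to hospital (+/- 1 day"), that is, days 8 to 10.

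Section 14 (Acute stroke therapy) covers patients who deteriorate, with ventilation as its example. If treatment or testing is not feasible, "testing should be performed one day later, if still within timeframe, otherwise testing should be cancelled". The next sentence makes an exception for the last in-hospital test: "The final testing (visit 3) should then be performed as soon as the patient is testable again (if timeframe >day 10"). It adds that this applies even to a patient who has had fewer than seven sessions. Section 12.1 says that every patient will have had seven sessions before the day-9 test.

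On scoring, Section 10.1 gives each TCT item a bottom category: "0= unable to perform movement without assistance". On analysis, Section 11.2 says "We plan an intention to treat analysis" and names the Mann-Whitney U test for the primary endpoint. On discharge, Section 8.2 says only that day 9 was chosen "because this is the mean residence time of stroke patients in the acute clinic before discharge to a rehabilitation center".

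**The concern.** Section 14 states a rule; it does not merely leave a gap. For one group of patients it replaces a fixed assessment time with an open one, and that group is defined by getting worse after randomisation, which treatment could influence. The sickest patients are measured only once they are well enough to be measured. Section 1 describes about a month of heightened plasticity after stroke, in which most recovery from impairment occurs, so extra days are likely to matter.

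The protocol does not say who decides that a patient is testable again. Section 7 says that all in-hospital assessors know the allocation.

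If one arm has more deteriorations, the primary comparison may fail to show it. A patient who dies before testing never contributes a TCT value. The mRS has a category for death and the primary outcome has none, although the analysis is declared to be by intention to treat.

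**Working it through.** The protocol has no calculated figure to reproduce. Section 11.1 sets 40 patients (20 per arm) on feasibility grounds, without a standard deviation, power or significance level. The check is therefore a comparison of passages, followed by illustrations on stated assumptions.

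**1. Passages side by side**

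- Time: days 8 to 10 (Sections 8.1 and 9) against any day after day 10 (Section 14).
- Sessions: seven for all before the test (Section 12.1) against possibly fewer (Section 14).
- Within Section 14: out-of-window testing is cancelled ("otherwise testing should be cancelled"), yet the final test is done out of window. The natural reading is that cancellation applies to the earlier tests only, but the text does not say so.
- Section 14 calls this test visit 3. Because the rule turns on day 10, it must mean Test 3, the primary assessment.
- Section 14 does not say whether the late value counts as the day-9 value.

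**2. Shift in an arm mean**

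If k of 20 patients in an arm are tested late and score d points higher than they would have at day 9, the arm's mean change shifts by k × d / 20. Both k and d are assumptions; 37 is 12 + 25 and 50 is 25 + 25 on the item scores.

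- k = 1, d = 12: 1 × 12 / 20 = 0.6
- k = 1, d = 37: 1 × 37 / 20 = 1.85
- k = 1, d = 50: 1 × 50 / 20 = 2.5
- k = 2, d = 37: 2 × 37 / 20 = 3.7
- k = 2, d = 50: 2 × 50 / 20 = 5.0

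For scale, Section 11.2 calls 12 points meaningful, and 5.0 / 12 = 42%. This is a rough yardstick only, because that section justifies 12 points by an individual patient's gain in independence.

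**3. Effect on the planned test**

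The Mann-Whitney test was simulated with 20 per arm, 4,000 runs and a two-sided 5% level (assumed). There was no treatment effect in the other patients, and k deteriorated patients were placed in one arm only. Four independent items scored 0, 12 or 25 with assumed probabilities 0.55, 0.30, 0.15 at baseline and 0.35, 0.35, 0.30 later.

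| k | Rejection if scored late as ordinary recoverers | Rejection if ranked worst |
|---|---|---|
| 1 | about 5% | 4.7% |
| 2 | about 5% | 6.6% |
| 3 | about 5% | 9.2% |
| 4 | about 5% | 14.7% |

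Late scoring leaves the test blind to the imbalance. Worst ranking makes it visible, though weakly at this sample size.

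**4. Why a score of 0 is not enough**

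The endpoint is a change. A patient with baseline 0 who dies and is assigned 0 has change 0 − 0 = 0, level with a stable survivor and above a survivor who worsened.

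**5. Discharge before day 8**

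The mean of 9 days is from Section 8.2; its spread is not given.

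- Normal stay: P(<8) = Φ((8 − 9)/SD). SD 2, 3, 4 gives 31%, 37%, 40%, or about 12 to 16 of 40.
- Lognormal stay: σ² = ln(1 + SD²/81), μ = ln 9 − σ²/2, P(<8) = Φ((ln 8 − μ)/σ). SD 3, 4, 6 gives 42%, 47%, 54%.

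The cited mean is for stroke patients in general, and the trial enrols severe hemiparesis, so the share may be smaller. These figures show only that the silence may matter.

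**The case against.** The strongest reply is that Section 14 governs data collection, and that treatment of late values and deaths is commonly left to a statistical analysis plan, which is not at hand. Testing patients whatever number of sessions they received is itself in keeping with intention to treat. Deterioration is also looked at elsewhere: complications to day 9 by Fisher's exact test, review of deaths and in-hospital serious adverse events, and blinded day-90 mRS with a category for death. Scoring uses one physiotherapist from each group.

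Part of this stands. Collecting a late test is not wrong, and the protocol does not say that it replaces the day-9 value. But the protocol itself contradicts its endpoint definition and its session statement, and that needs correcting whatever an analysis plan says. The other analyses do not repair the primary comparison. Paired scoring protects the score, not the decision on when to test.

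A reader might infer more than the text supports:

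- That early leavers are not tested. No passage says so. The protocol is silent, and seven daily sessions from day 2 run to day 8 (2 + 7 − 1), so the schedule appears to assume that patients stay.
- That the outcome has no common time. Days 8 to 10 apply to everyone except patients who cannot be tested then.
- That deterioration is scored as recovery. The late score is whatever the patient achieves, and it may be low or below baseline.
- That the rule inflates false positives. The simulation shows rejection staying near 5%; it supports masking only.

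**Conclusion.** The concern holds in a limited form. The final-test rule in Section 14 contradicts Sections 8.1 and 9 on time and Section 12.1 on sessions. Followed as written, it ties the timing of the primary outcome to a post-randomisation event, and it leaves patients who die without a primary value.

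The size cannot be read from the protocol. With one or two affected patients in an arm of 20, each gaining 37 to 50 points over the day-9 state, the arm mean shifts by about 1.9 to 5.0 points; with one patient gaining 12 it shifts by 0.6. These figures assume the number, the gain and that all affected patients are in one arm. In a pilot of 40, one or two such patients may be all there are, and the simulation shows little difference between the two scoring rules at that count.

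The silence on discharge before day 8 is a secondary point of unknown extent.

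**What to change.** 1. Reconcile Section 14 with Sections 8.1, 9 and 12.1 on both test timing and number of sessions, and say to which tests cancellation applies.
2. Keep days 8 to 10 as the window for the primary value, with discharge before day 8 (item 5) as the only stated exception.
3. State that patients who cannot be tested by day 10 because of deterioration, or who have died, receive the worst rank in the Mann-Whitney test of TCT change, rather than a score of 0.
4. Record the date of any later test and use it only in a sensitivity analysis.
5. For patients discharged before day 8, state that Test 3 is done on the last hospital day, with its date recorded and a sensitivity analysis for the earlier timing.

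The cost is protocol wording; no extra test is added. There are two drawbacks. Worst rank is an assigned value and not an observed one, whereas Section 10.1 wants the score to reflect performance in the test alone. Early-discharge values come sooner than day 8, and discharge also follows randomisation. Sensitivity analyses can show how much either matters.

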## **15. Funding**

This study is financially supported by a grant (8.600€) from the Hermann and Lilly Schilling foundation for medical research (Hermann und Lilly Schilling Stiftung für medizinische Forschung).

